## Abstract

**Background:**

Multiple factors combine to support a compelling case for interventions that target the development of obesity-promoting behaviours (poor diet, low physical activity and high sedentary behaviour) from their inception. These factors include the rapidly increasing prevalence of fatness throughout childhood, the instigation of obesity-promoting behaviours in infancy, and the tracking of these behaviours from childhood through to adolescence and adulthood. The Infant Feeding Activity and Nutrition Trial (INFANT) aims to determine the effectiveness of an early childhood obesity prevention intervention delivered to first-time parents. The intervention, conducted with parents over the infant's first 18 months of life, will use existing social networks (first-time parent's groups) and an anticipatory guidance framework focusing on parenting skills which support the development of positive diet and physical activity behaviours, and reduced sedentary behaviours in infancy.

**Methods/Design:**

This cluster-randomised controlled trial, with first-time parent groups as the unit of randomisation, will be conducted with a sample of 600 first-time parents and their newborn children who attend the first-time parents' group at Maternal and Child Health Centres. Using a two-stage sampling process, local government areas in Victoria, Australia will be randomly selected at the first stage. At the second stage, a proportional sample of first-time parent groups within selected local government areas will be randomly selected and invited to participate. Informed consent will be obtained and groups will then be randomly allocated to the intervention or control group.

**Discussion:**

The early years hold promise as a time in which obesity prevention may be most effective. To our knowledge this will be the first randomised trial internationally to demonstrate whether an early health promotion program delivered to first-time parents in their existing social groups promotes healthy eating, physical activity and reduced sedentary behaviours. If proven to be effective, INFANT may protect children from the development of obesity and its associated social and economic costs.

**Trial registration:**

Current Controlled Trials ISRCTN81847050

## Background

Preventing the development of obesity in children is an international health priority [1]. Current estimates suggest that the prevalence of overweight and obesity in all age groups is rapidly increasing worldwide [2]. In Australia approximately 25% of children are overweight or obese and that estimate is growing with data highlighting that these increases begin in early childhood [3]. An Australian sample of 114,669 pre-schoolers showed the prevalence of overweight and obesity increased from 16.3 to 27.2 per cent in girls and from 13.4 to 21.4 per cent in boys between 1995 and 2002 [4].

Overweight and obesity are recognised to have numerous negative impacts on children's health and wellness during childhood and through to adult life [5,6]. Further, research has shown that adiposity within the childhood period is a stable trait [7] and that parents are often poor at identifying fatness in their children [8]. In addition, obese children tend to become obese adults and treatment is difficult and costly [2]. Cochrane reviews have established that opportunities for prevention are poorly understood [9]. Overall there is an urgent need for research on the capacity to influence the development of children's obesity- promoting behaviours in early life.

Overweight in early childhood is determined in part by eating, physical activity and sedentary behaviours learnt at home in the first five years of life. The intervention outlined is informed by the understanding that (a) obesity-promoting behaviours are established early in life, (b) parents play a primary role in shaping these behaviours in infancy, (c) intervening before these behaviours (and parents responses to them) are established is likely to be effective, and (d) that the social milieu provided by parent groups is likely to facilitate and support the uptake of health promotion messages.

### Obesity-promoting behaviours are established early in life

Recent evidence highlights that obesity-promoting dietary habits, such as high consumption of energy-dense foods and fluids, previously documented in children [10,11] are also evident in infants and toddlers [12]. Australian data using 3-day weighed food records (n = 538), shows 90% of 18-month old children consumed energy-dense snack foods on the recall days and 70% consumed sweetened non-milk drinks (e.g. soft drinks) [13]. Overall, foods considered as "extra" or "non-core" provided 27% of the total energy intake in that sample. In addition, the nutritional quality of diet is known to continue to decline throughout childhood and adolescence [14,15].

These early dietary patterns couple with evidence of high levels of sedentary behaviours in early childhood. For example, 17% of 0–11 month and 48% of 12–23 month old children in the US watch more than the recommended two hours of television per day, and this proportion increases throughout childhood [16]. Further evidence suggests that viewing television for more than two hours per day is positively associated with obesity-promoting dietary behaviours and low levels of physical activity in young children [17,18]. Little physical activity trend data during infancy and early childhood is available, however it appears that physical activity levels fall throughout this period [19,20].

In addition to population trend data, there is evidence of tracking of children's dietary [21], sedentary and physical inactivity behaviours [22] from childhood to adolescence and adulthood, which appear to impact on adult health [23]. Thus, the obesity-promoting behaviours learned and supported during these early years may establish lifestyle behaviours that will track throughout the lifespan. Given this, it is reasonable to posit that early childhood provides a unique and circumscribed opportunity within which to establish lifestyle behaviours that will promote health and minimize the risk of the development of obesity.

### The role of parents in the promotion of children's behaviours

One of the most powerful predictors of weight management in overweight children is parental involvement, yet there remains an urgent need to examine opportunities to prevent childhood overweight and obesity via parental involvement in the early years [24-26]. Children's eating, physical activity and sedentary behaviours are learnt and sustained in the home and there is evidence that this environment impacts on children's weight [27,28]. Parents have the capacity via their nutrition knowledge, parenting style, modelling and the food environment to impact on children's emerging food choices [27]. Evidence has shown that in a young population (2–6 year olds, n = 564) the strongest predictor of children's fruit and vegetable consumption was parent consumption [29]. In addition, child rejection of fruits and vegetables (negative association) was modifiable with repeated exposure to rejected foods.

In terms of parents' involvement in physical activity with their children, one study reports that parents spend 13% of their child's play time in active play with their infant and that the remainder of time is spent in object play [30]. The use of parks and outdoor spaces is reported by less than half of parents with 5–12 year olds [20]. Children whose parents are active with them are reported to have higher levels of physical activity [31,32]. However, family rules are reported to be inversely associated with children's physical activity [26]. Similarly, rules prohibiting television viewing during mealtimes are reported to be inversely associated with children's television viewing time, and frequency of parent's watching television with their child has been found to be positively associated with children's television viewing [33].

Despite these trends, first-time parents may be particularly receptive to knowledge and skill development around parenting and the promotion of healthy family eating and physical activity behaviours. First-time parents regularly seek advice during their child's first year of life. In Victoria Australia, families make approximately 35 visits to health care providers for their infants during this first year [34]. Importantly, most visits to health service providers are not related to child illness, but rather reflect parental need for support and information during this period of rapid transition. In addition, parents indicate high levels of concern regarding children's appetite, eating patterns and growth, and regularly express the need for more comprehensive guidance in these areas [35]. It is likely that messages delivered to first-time parents may be preferentially received if delivered at times in their child's development when they are actively seeking strategies to manage emerging behaviours, an approach known as anticipatory guidance.

### Utilisation of anticipatory guidance

Anticipatory guidance is heralded as a promising approach by which health practitioners might support parents to promote healthy weight in their children by being proactive, informing parents about what to expect and how to manage behaviour, as opposed to supporting parents to manage events after they occur [36-38]. Anticipatory guidance has been shown to be effective across a range of domains, including parent-infant interactions, sleep patterns, injury prevention and reading at home [39].

Despite the promise of anticipatory guidance as an educative approach, just one study utilising this approach in the area of childhood eating has been published [40]. That study involved guidance of parents of new-borns regarding delaying introduction of solids. Compared to controls, the intervention resulted in positive differences in the types of foods introduced and increased confidence in health professionals as primary providers of information.

A randomised-controlled trial targeting overweight indigenous mothers of 1–3 year olds focused on parenting skills to promote improved child eating and physical activity patterns [41]. That study found intervention group infants had decreased relative weight, total energy intake, and improved parent-child interactions around food over 16 weeks. This high quality US study highlights that parents are willing and capable of making positive changes to improve their child's health and body weight.

### INFANT: preventing childhood obesity and promoting healthy life-style choices

The INFANT project will employ an anticipatory guidance approach to support first-time parents attending a new parents' group to be skilled in their approaches to their infant's emerging dietary, physical activity and sedentary behaviours. The intervention will be delivered by an experienced dietitian during infants' first 18 months of life at first-time parents groups held within Maternal and Child Health (MCH) centers. Evidence supports the proposition that education regarding lifestyle behaviours is feasible within existing MCH infrastructures and that it is likely to be effective [42,43]. Victoria's 80 MCH Centres (across 39 regions) are a cornerstone of service provision with 96% of all first-time parents attending [34]. MCH nurses routinely establish first-time parents' groups through which education sessions are delivered. A recent prospective study [43] reported that 2/3rds of eligible first-time mothers joined these groups and that of these groups, 2/3rds were still meeting 18 months after the formal sessions had concluded. Drop out from such groups was estimated to be between 10 and 15%. That study also documents the important social environment that first-time mothers' groups provide throughout this early period of parenting. Given the stability of these pre-existing groups and the well-documented capacity of groups to support and reinforce the uptake of knowledge and skills we propose that these groups will provide an important vehicle by which we may deliver an intervention. In addition, our pilot work and engagement with local government areas has demonstrated that access to these groups via MCH nurses is feasible and that willingness of mothers within these groups to participate in research is high.

While this intervention utilises professional support beyond that currently existing in MCH Centres, it remains modest in terms of total cost of implementation and is designed for long-term sustainability, with skills required easily transferable to MCH nurses and other comparable health professionals.

The intervention draws on parenting support theory [44], which emphasizes children's psychological and behavioural goals, logical and natural consequences, mutual respect and encouragement techniques. Emphasis will be placed on parents' understanding of how improved parenting skills can facilitate the development of appropriate eating and activity behaviours in children. In the feeding domain, these approaches have been operationalised by Satter who promotes the 'Division of Responsibility in Feeding' [45] This approach has also been adopted in the US Start Health Feeding Guidelines for Infants and Toddlers [46]. Havery-Berino et al [47] report, in one of the only relevant studies in this age group (age 9 to 36 months), a positive impact on children's dietary intakes using similar approaches.

The intervention will use an anticipatory guidance framework, to coincide with opportunities to support parents regarding feeding, physical activity and sedentary behaviour issues for infants prior to their evolution. In addition, it will utilise the dynamics of existing first time parents' groups to support and reinforce the messages delivered in the intervention.

## Aims and Hypotheses

The aim of the study is to test the effectiveness of an early childhood obesity prevention intervention delivered to first-time parents and focussed on parenting skills which support the development of positive diet and physical activity behaviours, and reduced sedentary behaviours in infants from 3 to 18 months of age.

### Study hypotheses

In comparison to the control group infants, over the course of the intervention, the intervention group infants will:-

• Demonstrate greater increases in consumption of fruits and vegetables, and smaller increases in consumption of cordials, soft-drinks and juices and energy-dense snack foods.

• Demonstrate greater increases in time spent being physically active and smaller increases in time spent in sedentary behaviours, specifically TV viewing.

• Exhibit reduced incremental BMI gain.

In comparison to the control group parents, the intervention group parents will demonstrate greater increases in:-

• the frequency with which they offer fruit and vegetables, water and milk (rather than cordials, soft-drinks and juices); and smaller increases in the frequency with which they offer energy-dense snack foods to their child;

• knowledge regarding infant eating, physical activity and sedentary behaviours and greater development of positive attitudes/beliefs regarding their capacity to influence these behaviours.

• the adoption of desired feeding strategies, including the division of responsibility in feeding and in providing opportunities for modelling of healthy eating.

• the adoption of strategies, including modelling, for increasing opportunities for physical activity and reducing opportunities for sedentary behaviours.

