### Randomization

First-time parents groups will be randomised after recruitment in order to ensure baseline equivalence and minimise selection bias. Within each local government area, first-time parents groups will be randomly allocated to the intervention or control group in order of recruitment, using a computer generated random number schedule developed by a statistician who has no contact with the centres. Prior to the first intervention session families will be informed by letter regarding the outcome of randomisation.

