### Measures

Parent and infant data will be collected using parent self-completion questionnaires, apart from infant dietary intake data which will be collected by telephone interview. As outlined in Table 2, all data (appropriate to the age of the child) will be collected every three months, corresponding with the six intervention sessions. Repeated data collection is necessary given the rapid changes in height, weight, eating and activity behaviours in infants. The measures collected are detailed below.

**Table 2 T2:** Measures and time-frame for the study

Intervention timeline – year		1		2			3
Measures		Infant Age					
		3 months	6 months	9 months	12 months	15 months	18 months

Dietary Intake	Parent	✓					✓
	Child	✓	✓	✓			✓
Sedentary behaviour	Parent	✓					✓
	Child			✓			✓
Physical activity	Parent	✓					✓
	Child		✓	✓	✓	✓	✓
Family Food Environment	Parent	✓		✓			✓
Family physical activity & Sedentary Environment	Parent	✓		✓			✓
Demographic Data	Parent	✓					
Anthropometric Data	Parent	✓					✓
	Child	✓	✓	✓	✓	✓	✓

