### Data analysis

All analyses will be conducted using the intention to treat principle. Generalized Estimating Equations (GEE) [57] will be used to fit regression models to describe the effects of the intervention on key outcome variables among parents and infants. Separate models will be fitted, to determine differences in key outcome variables in the intervention and control groups.

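### Infant BMI and parent outcomes are framed as gains without saying how the 3-month values enter the models, and the stated timings allow self-reported baselines to follow disclosure of the arm

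*Protocol article*

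**What the plan says.** **Hypotheses.** The Study hypotheses section expects intervention infants to "Exhibit reduced incremental BMI gain". For parents it states: "In comparison to the control group parents, the intervention group parents will demonstrate greater increases in", followed by the offering of foods, knowledge and attitudes, feeding strategies, and activity strategies.

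**Analysis.** The Data analysis section says that GEE "will be used to fit regression models to describe the effects of the intervention on key outcome variables among parents and infants", and then: "Separate models will be fitted, to determine differences in key outcome variables in the intervention and control groups". It does not name the response as a gain or as a follow-up value, and it names no covariates.

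**Measurement.** Table 2 in the Measures section marks child "Anthropometric Data" at all six ages from 3 to 18 months. It marks "Family Food Environment" and the family activity and sedentary environment at 3, 9 and 18 months, and parent diet and physical activity at 3 and 18 months. Parents complete questionnaires themselves, while trained staff take length, height and weight.

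**Timing.** The Measures section says that data "will be collected every three months, corresponding with the six intervention sessions". The Randomization section says that groups are randomised after recruitment, and adds: "Prior to the first intervention session families will be informed by letter regarding the outcome of randomisation".

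**The concern.** There are two separate issues, both about the 3-month value.

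**Use of the baseline.** The hypotheses are the article's only description of what is compared, and they speak of gains. If gain is taken over literally as the response, the comparison is less precise than one of 18-month values adjusted for the 3-month value. For BMI, raw gain also carries variation from age and sex. The Measures section itself notes that infant size changes quickly, and measurement is tied to group session dates rather than to each infant's exact age.

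**Timing of the baseline.** A baseline serves as a reference only if allocation cannot influence it. A parent who already knows that the group will receive a feeding and activity programme may answer questions on knowledge, feeding style or the home environment differently. A shift in a self-reported baseline then enters the comparison between arms, and no later analysis plan can remove it.

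**Working it through.** **1. The plan's own sample size.** The inputs come from the Sample size section: mean 32 g, SD 15 g, a 25% increase (0.25 × 32 = 8 g), cluster size 10, intracluster correlation 0.2, attrition 40% and oversampling 15%. Alpha and power are not given there, so I assume two-sided 5% and 80%.

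- Per arm: 2 × (15 × (1.960 + 0.842) / 8)² = 55.2, rounded up to 56, so 112 in total, as stated.
- Design effect: 1 + (10 − 1) × 0.2 = 2.8, as stated.
- Total: 112 × 2.8 = 313.6; 313.6 / 0.60 = 522.7; 522.7 × 1.15 = 601, against the stated 600.

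This calculation uses an 18-month mean and SD for vegetable intake. It involves no gain and no correlation with baseline, so nothing below changes it.

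**2. Gain against baseline adjustment.** Let r be the correlation between the 3- and 18-month values. The article gives no r, so the range is assumed. With equal variances at the two ages, and taking the variance of an 18-month-only comparison as 1:

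- unadjusted change score: 2(1 − r)
- 18-month value adjusted for the 3-month value: 1 − r²
- ratio, adjusted to change: (1 − r²) / (2(1 − r)) = (1 + r)/2

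| r (assumed) | Change | Adjusted | Ratio | Excess standard error of change |
|---|---|---|---|---|
| 0.3 | 1.40 | 0.91 | 0.65 | 24.0% |
| 0.5 | 1.00 | 0.75 | 0.75 | 15.5% |
| 0.7 | 0.60 | 0.51 | 0.85 | 8.5% |
| 0.9 | 0.20 | 0.19 | 0.95 | 2.6% |

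The last column is √(1/ratio) − 1. The benefit shrinks towards nothing as r approaches 1.

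**3. Order of events.**

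- Recruitment comes first, then randomisation, then the letter, then session 1 (Randomization).
- Session 1 is at 3 months of age (Table 1).
- The first data collection is also at 3 months and is tied to the sessions (Measures and Table 2).

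If the 3-month data are taken at session 1, the letter has already arrived. If they are taken at recruitment, it has not. The text allows both, although the link to the sessions makes the first the more natural reading.

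**4. What a shifted baseline would do.** Suppose knowledge of the arm moves the mean self-reported baseline in one arm by δ. A change-score comparison absorbs −δ in full. The adjusted comparison subtracts b times the baseline difference, and b = r when the variances are equal, so it absorbs −rδ: 0.3δ to 0.7δ in size for r from 0.3 to 0.7. Adjustment therefore reduces the problem but does not remove it; the order of events has to be fixed. The documents give no basis for the size or sign of δ.

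**The case against.** **The analysis text is open.** A hypothesis about gain describes an expected effect, not an estimator. The GEE sentences are compatible with a baseline covariate or with a group-by-time model, and an article commonly leaves covariates to a fuller document. This stands. A reader might infer that the trial will analyse change scores and leave the baseline out, but the article says neither. What remains is a recommendation on how to make the comparison that the hypotheses describe.

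**The arithmetic is simplified.** The ratio assumes two time points, equal variances and independent individuals. Here parents are clustered, child anthropometry is taken six times and the family environment measures three times. This also stands. A reader might invert the ratio (1/0.85 = 1.18 and 1/0.65 = 1.54) and claim the equivalent of 18% to 54% more participants; that does not carry over directly to this design.

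**Raw BMI gain is not biased.** Groups are randomised and both arms follow the same age schedule, so age and sex balance in expectation. This is correct: standardisation is about noise and interpretation, not validity.

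**The order of baseline and letter is not stated.** Linking collection to sessions may only align calendars, randomising after recruitment leaves room for an earlier baseline, and the study design figure is not shown. A reader might infer that the baseline does follow disclosure; the text permits this but does not state it. The argument also has little force for BMI, which staff measure. It still holds that no section places the questionnaires before the letter, and that randomising after recruitment does not protect a self-report completed after disclosure.

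**Conclusion.** The point holds as a recommendation in two parts.

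**Precision.** Where a 3-month value exists, the 18-month comparison adjusted for it is preferable to raw gain. Its variance is 0.65 to 0.85 of that of an unadjusted two-point change score, for r of 0.3 to 0.7. This rests on an assumed r and equal variances, and it is illustrative for a clustered trial with repeated measures. An unadjusted change score would still be valid under randomisation with an undisturbed baseline, and the target of 600 stands.

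**Timing.** The Randomization and Measures sections together allow self-completed parent baselines to be collected after families learn their arm. The possible bias concerns parent-reported knowledge, feeding and home environment, and its size cannot be derived from the documents. This part is the more pressing, because it cannot be repaired once the baselines have been collected.

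**What to change.** 1. In Data analysis, state that 18-month values are compared between arms with the 3-month value as a covariate in the GEE model, instead of raw gain. Apply this to child anthropometry, the family food environment, the family activity and sedentary environment, and parent diet and activity.
2. For infant growth, use BMI standardised for age and sex at both ages.
3. In Randomization and Measures, require the 3-month questionnaires and measurements to be completed before the allocation letter is sent.

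The cost is one covariate per model, a standard transformation of BMI, and a small scheduling constraint between baseline collection and the letter. No new data are needed and the sample size does not change.

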#### Dietary intake

Dietary intake for mother and father will be assessed using The Cancer Council's Dietary Questionnaire for Epidemiological Studies (Version 3) at baseline and study conclusion. This questionnaire is an updated version of the semi-quantitative food frequency questionnaire specifically developed for the Melbourne Collaborative Cohort Study [49]. Child's dietary intake will be assessed by telephone-administered multi-pass 24-hour recall with parents [50]. Visual aids will be provided to primary carers in advance of interviews to help in the estimation of quantities of food consumed. Three days of dietary data will be collected (including one weekend day) when the infant is 9 and 18 months of age.

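### Child BMI and parent outcomes are framed as gains from baseline, and the analysis names no baseline term; adjusting for the 3-month value would be more precise at almost no cost

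*Protocol article*

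**What the plan says.** In the protocol article, Study hypotheses, the parent hypotheses open with "In comparison to the control group parents, the intervention group parents will demonstrate greater increases in" and go on to what parents offer their child, their knowledge and attitudes, their feeding strategies and their activity strategies. (Energy-dense snacks are worded as a smaller increase in offering.) The infant adiposity hypothesis reads "Exhibit reduced incremental BMI gain". The Sample size section also describes its target as detecting changes.

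The Data analysis section says that GEE "will be used to fit regression models to describe the effects of the intervention on key outcome variables among parents and infants", and then: "Separate models will be fitted, to determine differences in key outcome variables in the intervention and control groups". It mentions neither a change score nor a baseline covariate.

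Table 2 (Measures) ticks child anthropometry at 3, 6, 9, 12, 15 and 18 months. It ticks the family food environment and the family physical activity and sedentary environment at 3, 9 and 18 months.

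**The concern.** There are three usual ways to handle a baseline in a two-arm comparison: subtract it, ignore it, or adjust for it. In a randomised trial all three estimate the same expected arm difference, but not with the same precision. Subtraction gives the baseline a fixed weight of 1. Ignoring it gives it a weight of 0. Adjustment estimates the weight from the data.

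The hypotheses lean towards subtraction. The analysis section, read literally, allows subtraction or no use of the baseline at all. Either would give wider confidence intervals than the data allow. Either would also leave the result more exposed to chance baseline differences between arms, with about 60 randomised groups (600 parents at about ten per group). The outcomes concerned are BMI, the only adiposity outcome among the hypotheses, and the parent outcomes through which the programme is meant to work.

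**Working it through.** **The plan's own figure.** The Sample size section gives a mean of 32 g/day, an SD of 15 g and a 25% increase, so the difference is 0.25 × 32 = 8 g. With two-sided 5% and 80% power (not stated, assumed here), this gives 56 per arm, 112 in total, as stated. The design effect is 1 + (10 − 1) × 0.2 = 2.8. Then 112 × 2.8 = 313.6; 313.6 / 0.60 = 522.7; 522.7 × 1.15 = 601, against 600 stated. The figure reproduces. It uses an 18-month cross-sectional SD, so it does not depend on how a baseline is handled.

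**Inputs for the comparison.** Let s be the SD at 18 months, k·s the SD at 3 months, and r the correlation between the two. The article gives neither k nor r. I take k = 1 and r from 0.3 to 0.9.

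**Variances, relative to s².**
- Unadjusted 18-month value: 1
- Change from 3 months: 1 + k² − 2rk, which is 2(1 − r) when k = 1
- 18-month value adjusted for the 3-month value: 1 − r²

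With k = 1, adjusted over change is (1 − r²) / [2(1 − r)] = (1 + r)/2.

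| r (assumed) | Change | Adjusted | Adjusted / change | Adjusted / unadjusted | SE of change vs adjusted |
|---|---|---|---|---|---|
| 0.3 | 1.40 | 0.91 | 0.65 | 0.91 | 24% larger |
| 0.5 | 1.00 | 0.75 | 0.75 | 0.75 | 15% larger |
| 0.7 | 0.60 | 0.51 | 0.85 | 0.51 | 8% larger |
| 0.9 | 0.20 | 0.19 | 0.95 | 0.19 | 3% larger |

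The two alternatives fail at opposite ends. At low r, change is the costly choice, and below r = 0.5 it is worse than ignoring the baseline. At high r, ignoring the baseline is the costly choice. Adjustment is the most precise of the three throughout.

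**Clustering.** A simulation of 60 groups of ten with ICC 0.2, and the same r within and between groups, gave adjusted/change variance ratios of 0.66, 0.76 and 0.84 at r = 0.3, 0.5 and 0.7. The formula gives 0.65, 0.75 and 0.85, so it carries over to the clustered design.

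**Unequal SDs.** Change variance minus adjusted variance is (1 + k² − 2rk) − (1 − r²) = (k − r)². This is never negative, so adjustment does not lose to change. It is small when k and r are both small, as for the offering of solid foods at 3 months, when values sit near a floor. For example, k = 0.2 and r = 0 gives 1.04 against 1.00.

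**The case against.** The strongest reply is that a hypothesis is not an estimator. Under randomisation the expected arm difference in change equals the expected arm difference at 18 months, so a baseline-adjusted GEE model tests the hypotheses as worded. The Data analysis section does not rule that model out, and the sample size uses an 18-month SD rather than an SD of change. A condensed article may also leave covariates to a fuller document. This stands to the extent that a reader might infer a plan fixed on raw change scores; the article never says so, and the loss is conditional. What remains is that the only contrasts in print are worded as change and the models in print have no baseline term. Both natural readings are therefore less precise than a third that uses data already collected.

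Other stronger readings also fail:
- Parents' own diet is measured "for Epidemiological Studies (Version 3) at baseline and study conclusion", and Table 2 also has their activity and sedentary behaviour at 3 and 18 months. A reader might count these among the affected hypotheses, but Study hypotheses states none on parents' own intake, activity or viewing time.
- The child behaviour outcomes do not fit the point well. Table 2 starts child physical activity at 6 months and child sedentary behaviour at 9 months. The text places the child diet recalls "when the infant is 9 and 18 months of age", although Table 2 also ticks 3 and 6 months.
- The Background names parental intake as the strongest predictor of children's fruit and vegetable intake ("fruit and vegetable consumption was parent consumption"). That comes from 2–6 year olds with no correlation given, so no gain from using it as a covariate can be shown here.
- Quoting only low correlations would overstate the loss from change scores. The Background calls childhood adiposity stable, so a high r for BMI cannot be excluded.
- BMI is measured six times, so a repeated-measures analysis is possible, and the two-point formula does not describe it fully.

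**Conclusion.** The point holds as a conditional, minor one. If child BMI and the hypothesised parent outcomes are analysed as change from 3 months, the variance is 1/((1 + r)/2) times that of the baseline-adjusted estimate: about 1.54, 1.33, 1.18 and 1.05 times at r = 0.3, 0.5, 0.7 and 0.9. If they are analysed as unadjusted 18-month values, it is 1/(1 − r²) times. These figures rest on an assumed r and equal SDs at the two ages. The true size cannot be fixed from the article, and the cost of change scores is small for outcomes near a floor at 3 months. No stated number is wrong and the sample size is unaffected. The case for acting is that the gain costs almost nothing and that stating the model in advance removes a later choice between estimates.

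**What to change.** In the Data analysis section, state that for child BMI, and for each hypothesised parent outcome with a 3-month value in Table 2, the GEE model compares arms on the 18-month value with the participant's own 3-month value as a covariate. State also that this model tests the hypotheses worded as increases and gain, so the Study hypotheses section need not change. The intermediate BMI measurements may enter the same model as further repeated outcomes, with the arm difference still read at 18 months.

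The cost is one or two sentences and one extra covariate per model. No new data, visits or participants are needed, and the downside is nil to small.
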